# Effects of salvianolate on microcirculatory disturbance in patients with stable coronary heart disease: study protocol for a randomized controlled trial

**DOI:** 10.1186/s13063-021-05099-7

**Published:** 2021-03-08

**Keywords:** Salvianolate, Coronary microcirculation

## Abstract

**Background:**

Obstruction of coronary microcirculation can lead to myocardial ischemia and poor prognosis. Salvianolate exerts cardiovascular protection at cellular levels. However, no studies have confirmed the effect of salvianolate on stable coronary heart disease (CHD) with high fractional flow reserve (FFR) and myocardial microcirculatory disturbances.

**Methods/design:**

This study will enroll 78 patients who have stable coronary disease with 50 to 70% stenosis in major coronary arteries and whose FFR > 0.80 and index of microcirculatory resistance (IMR) > 25. Patients will be randomly divided into the salvianolate group or the placebo group. After above evaluations, salvianolate 200 mg will be intravenously dripped immediately for the next 30 min and subsequent 7 days in the salvianolate group, and matching 0.9% normal saline will be arranged in the placebo group. IMR will be reevaluated in immediate phase after first 30 min of salvianolate or placebo treatment. The primary end point will be the IMR change in this phase, and the secondary end points will be the total ischemic burden assessed by the Seattle angina scale, quality of life scale, Holter electrocardiography, and 6-min walk test after 7 days before discharge.

**Discussion:**

This study will firstly clarify the improvement effect of salvianolate on coronary microcirculation and provide an effective treatment method for stable CHD patients with high FFR and myocardial microcirculatory disturbance.

**Trial registration:**

Chinese Clinical Trial Registry ChiCTR1800018772. Registered on 9 October 2018 and updated on 2 March 2020

## Background

Coronary microcirculatory disturbance is one of the most important causes of angina pectoris [1], and it is often difficult to be diagnosed and treated in clinical practice. Index of microcirculatory resistance (IMR) is a novel and relatively simple quantitative assessment method. It can truly reflect the microcirculatory function and is not affected by the epicardial artery stenosis. IMR is recognized as the best indicator to assess the coronary microcirculation damage [2–4]. The simultaneous assessment of fractional flow reserve (FFR) and IMR in patients with critical coronary lesions can clarify the causes of myocardial ischemia in stable coronary heart disease (CHD).

Obstruction of coronary microcirculation can lead to myocardial ischemia [5], significantly affecting the patients’ prognosis [6]. It has been found that angiotensin-converting enzyme inhibitors and sildenafil can improve the microvascular index of patients with microcirculatory disorders [7–9] while therapeutic effects of calcium antagonists and alpha blockers have been highly controversial [10, 11].

Salvianolate is a water-soluble effective active site of traditional Chinese herb salviae miltiorrhizae, and its main component is magnesium lithospermate B. Magnesium lithospermate B can protect the cardiovascular system via anti-oxidation, anti-inflammation, endothelial protection, myocardial protection, anticoagulation, vasodilatation, anti-atherosclerosis, and reducing the proliferation and migration of vascular smooth muscle cells [12, 13]. It can also reduce the incidence of contrast-induced nephropathy after percutaneous coronary intervention and is more effective than normal saline [14]. In addition, it has been confirmed that intravenous administration of salvianolate can improve cardiac microcirculatory perfusion and increase cardiac output in rats [15]. Similarly, continuous intravenous salvianolate 10 mg/kg/day for 7 days can significantly improve myocardial microcirculatory reflow in an ischemia-reperfusion minipig model, as well as reduce oxidative stress and myocardial apoptosis [16]. However, no studies have been conducted to verify the efficacy of salvianolate against coronary microcirculatory disturbance of CHD from the perspective of IMR.

Accordingly, in this study, we try to evaluate the effect of salvianolate intravenous infusion on IMR in stable CHD patients with high FFR and myocardial microcirculatory disturbance, as well as to evaluate the effect of short-term use of salvianolate on total ischemic burden in these patients.

## Methods/design

### Study design

This is a prospective, single-center, randomized, double-blind controlled study. We will enroll 78 stable CHD patients who have a 50 to 70% stenosis in major coronary arteries and whose FFR > 0.80 and IMR > 25. They will be randomly divided into the salvianolate group or the placebo group. The former group will be given intravenous salvianolate (200 mg salvianolate dissolved in 100 ml 0.9% sodium chloride injection, intravenous drip for 30 min) after the first measurement of IMR. The latter group will be intravenously given matching 0.9% normal saline 100 ml. Thirty minutes later, both groups will undergo reevaluation of IMR. For the subsequent 7 days, the salvianolate group will be intravenously infused with salvianolate 200 mg/day and the placebo group will continue to use matching 0.9% normal saline per day. Other medications will be used according to clinical needs. After 7 days, all patients will be assessed by the Seattle angina scale, quality of life scale, Holter electrocardiography, and 6-min walk test.

The trial protocol has been approved by the Institutional Ethics Committee of Sir Run Run Shaw Hospital of Zhejiang University and has been registered in the Chinese Clinical Trial Registry (ChiCTR1800018772). All patients will provide written informed consents before randomization.

### Inclusion and exclusion criteria

Seventy-eight stable CHD patients with 50 to 70% stenosis in major coronary arteries, FFR > 0.80, and IMR > 25 at Sir Run Run Shaw Hospital of Zhejiang University will be enrolled in this trial. Detailed inclusion and exclusion criteria are shown in Table 1. The attending physician of the patient is responsible for inclusion and exclusion assessment.

**Table 1 Tab1:** Inclusion and exclusion criteria

Inclusion criteria	Exclusion criteria
• Angina pectoris • CAG showed 50 to 70% stenosis in major coronary arteries; FFR > 0.8, IMR > 25; • Patients received no salvianolate treatment previously.	• Patients with left main disease; • Patients with severe cardiac insufficiency (New York Heart Association grade III or higher), severe renal insufficiency (eGFR < 60 ml/min), liver dysfunction (ALT > 3 × URL), and asthma history; • Severe cerebrovascular disease; infection, hematopoietic dysfunction, tumor or mental illness; • Combined malignant arrhythmia or third degree atrioventricular block; • Currently taking other Chinese herbs for the treatment of angina; • Pregnant or breastfeeding women; • Currently participating in other clinical trials; • Allergic to known ingredients of salvianolate; and • The investigator considers it unsuitable for inclusion in other circumstances, or the patient or family members do not agree with the study’s treatment plan.

*CAG*, coronary angiography; *FFR*, fractional flow reserve; *IMR*, index of microcirculatory resistance; *eGFR*, estimated glomerulus filtration rate; *ALT*, alanine aminotransferase; *URL*, normal reference level

### Exclusion criteria during the follow-up periods

Patients who should not be enrolled but have been enrolled should be excluded. Patients who have received at least one dose of salvianolate or matching placebo but fail to complete the trial because of poor compliance or voluntary withdrawal should not be removed. Every withdrawal will be recorded in the case report forms (CRFs), and a visit will be arranged if possible. Although their data cannot be used for efficacy analysis, they can be used for safety analysis. The trial could be terminated in advance by investigators if there are any safety problems. Once it is terminated, all CRFs should be kept for future reference.

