Premature discontinuation of salvianolate, loss to follow-up, and death are possible intercurrent events. As we use treatment policy strategy in our study, we will take a per-protocol analysis, as well as intention-to-treat (ITT) analysis for statistical analysis. Per-protocol analysis includes participants who complete the assigned therapy according to the trial protocol while ITT analysis includes all randomly assigned participants according to the treatment group to which they were originally assigned, regardless of the occurrence of intercurrent events. The ITT analysis will indicate how salvianolate will work in a more real-life setting. If there is evidence that the difference in the treatment depends on certain patient characteristics identified in the baseline assessment, a subgroup analysis will be performed.

The missing data before the intercurrent events will be filled with the measured values of “similar participants.” The similar patients should have the same sex and smoking history (smoker or nonsmoker). Missing values will be imputed by expectation-maximization algorithm through age, systolic blood pressure, diastolic blood pressure, fasting blood glucose, and IMR. Multiple imputation will be used in our study. *P*-value < 0.05 will be considered to indicate statistical significance. All statistical analyses will be performed using the Statistic Package for Social Science (SPSS) software package, version 18.0 (SPSS Inc., Chicago, IL, USA). The results will be published by the chief investigator and major contributors.

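### The bar on efficacy use of non-completers' data, and the unlimited exclusion of wrongly enrolled patients, conflict with the promised ITT analysis and would discard Day 1 IMR values already measured

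*Protocol article*

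**What the plan says.** Two parts of the protocol article decide who counts for efficacy.

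**Exclusion criteria during the follow-up periods.** On eligibility errors: "Patients who should not be enrolled but have been enrolled should be excluded". No analysis set is named. Patients who received at least one dose but "fail to complete the trial because of poor compliance or voluntary withdrawal should not be removed" stay in the trial. Their withdrawal is recorded in the case report form, and a visit is arranged where possible. The section then adds: "Although their data cannot be used for efficacy analysis, they can be used for safety analysis".

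**Analysis.** "Premature discontinuation of salvianolate, loss to follow-up, and death are possible intercurrent events". The section continues: "As we use treatment policy strategy in our study, we will take a per-protocol analysis, as well as intention-to-treat (ITT) analysis for statistical analysis". The per-protocol set is the patients who complete their assigned therapy as the protocol requires. By contrast, "ITT analysis includes all randomly assigned participants according to the treatment group to which they were originally assigned, regardless of the occurrence of intercurrent events".

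**Timing.** Under Study design, End points and Table 2, the primary end point is the IMR change in the immediate phase. It is measured on Day 1 after the first 30-minute infusion. Seven further days of daily infusion follow, and the symptom scales, Holter and walk test come at their end.

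**The concern.** A patient who stops on, say, the third day must be in the ITT analysis under one section and may not enter an efficacy analysis under the other. Whoever writes the analysis code must break one of the two rules.

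What is at stake is the randomised comparison. Poor compliance and withdrawal happen after randomisation and can depend on treatment, for example through intolerance, relief or lack of relief. Removing such patients selects on those events. For the primary end point the removal also serves no purpose, because the outcome is complete before the behaviour that triggers it. The same Analysis section plans multiple imputation, so values never observed could be imputed while measured ones are barred.

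A per-protocol set defined by completing therapy has the same effect on IMR if it is read as completing the 7-day course: a Day 1 result is kept or dropped according to what happens later in the week.

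**Working it through.** **1. The rules side by side**

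| Patient | Exclusion section | ITT definition in Analysis |
|---|---|---|
| Dosed, repeat IMR obtained, leaves or complies poorly during the 7 days | Safety only | Included; discontinuation and loss to follow-up are listed intercurrent events |
| Dosed, leaves before the repeat IMR | Safety only | Included; repeat IMR is missing |
| Randomised, later found ineligible | Excluded, no set named | Included as randomised |

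All three rows conflict on who belongs in the analysis. Only the first, and any ineligible patient with a repeat IMR, involves discarding an observed primary outcome. Day 7 data obtained at the visit offered to withdrawn patients would be barred as well.

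**2. The plan's own sample size**

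Inputs from Sample size: α = 0.05, power 0.80, means 20 and 40, σ = 20, Δ = −8, loss 10%. The difference in the plan's formula is 20 − 40 + 8 = −12.

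n = 2(Zα + Zβ)²σ²/(difference)²

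- One-sided α: 34.35, so 35 per group (36 with the noncentral t).
- Two-sided α: 43.6, so 44 per group (45 with t), which does not match the plan.
- Loss: 35/0.9 = 38.9, so 39 per group and 78 in total. Starting from 36, 36/0.9 = 40 per group and 80 in total.

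The stated figures of about 36 per group and 78 in total are thus reproduced on a one-sided α of 0.05. The document does not state the sidedness, so both are shown below.

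**3. Power if patients are barred**

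The document gives no rate for the barred group, so the rate is an assumption. With fraction w barred equally in both groups, n = 39(1 − w) per group. One-sided power is Φ(12/(20√(2/n)) − 1.645); two-sided uses 1.960.

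| Assumed w | Patients barred of 78 | n per group | One-sided power | Two-sided power |
|---|---|---|---|---|
| 0 | 0 | 39 | 0.842 | 0.755 |
| 5% | 3.9 | 37.05 | 0.826 | 0.733 |
| 10% | 7.8 | 35.1 | 0.807 | 0.710 |
| 20% | 15.6 | 31.2 | 0.766 | 0.659 |

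These values inherit the plan's formula, which takes the 8-point margin off the assumed 20-point difference. A plain test of a 20-point difference needs only 13 per group (one-sided, same method), so its power would hardly be affected.

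**4. Bias**

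The document gives no withdrawal rates by group, no reasons for leaving and no IMR values for those who leave. Neither the size nor the direction of a bias can be calculated.

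**The case against.** The best defence is that the exclusion section was meant to describe only the per-protocol set. It keeps non-completers in the trial and records their data, and the statistical section states the ITT rule clearly. This reading is possible, but the text does not give it: the bar covers efficacy analysis without qualification, and the per-protocol set is defined elsewhere. If that was the intention, one clarifying line is still needed.

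Several stronger readings are tempting and should be resisted.

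- *The ITT analysis cannot be run.* It can. The patients and their data are kept; only the rule stands in the way.
- *About 8 of 78 patients would be lost, most with a valid IMR.* This equates the 10% loss rate, which the plan uses only to inflate N and does not define, with the barred group. No section makes that link, and how many barred patients would have a repeat IMR is not stated.
- *Treatment policy is offered as the reason for a per-protocol analysis.* The sentence names ITT as well. It is loosely worded, since a completers' set does not follow from treatment policy, but it does not stand for per-protocol alone.
- *Wrongly enrolled patients bring the same bias.* Their eligibility is mostly a baseline matter and the trial is double-blind, so selection on post-randomisation events does not fit them well. The conflict with the ITT definition remains.
- *No primary set is named, and death has no strategy of its own.* A full protocol or SAP commonly settles these, so neither counts as an error here.

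**Conclusion.** The point holds as a conflict between two printed rules, with an avoidable loss of observed primary outcomes if the exclusion section is followed. It rests on the text and on the timing of the end point, not on a figure. The loss concerns patients who leave after the repeat IMR; those who leave before it have no primary value to discard.

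The effect on power is modest: about 0.83 to 0.77 one-sided for an assumed 5% to 20% barred, and still 0.807 at 10%, a loss that N already allows for. The main harm is selection on events after randomisation, whose effect cannot be quantified from the document. The conflict should be resolved before analysis, because it decides who enters the primary comparison.

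**What to change.** 1. In the exclusion section, limit both rules (non-completers and wrongly enrolled patients) to the per-protocol set.
2. In Analysis, state that the treatment-policy (ITT) analysis includes all randomised patients as randomised and uses every 30-minute IMR obtained, whatever happens later in the week. Make the per-protocol analysis supportive.
3. For the IMR end point, define the per-protocol set by receipt of the Day 1 infusion and a valid repeat IMR, not by completing the 7-day course. Completion of the course can remain the criterion for the Day 7 end points.

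The cost is an amendment of wording, submitted to the ethics committee as the protocol requires. N stays 78 and no new data are needed.

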**End points**			
Seattle angina scale	X		X
Quality of life scale	X		X
Holter electrocardiography	X		X
6-min walk test	X		X
IMR	X	X	

*CBC*, complete blood count; *Scr*, serum creatinine; *BUN*, blood urea nitrogen; *UA*, uric acid; *K*, potassium; *Na*, sodium; *Cl*, chloride; *ALT*, alanine aminotransferase; *AST*, aspartate aminotransferase; *BIL*, bilirubin; *cTnT/cTnI*, cardiac troponin T/I; *IMR*, index of microcirculatory resistance

In the screening stage, the investigator conducts a baseline assessment and gets the informed consent and randomization. Coronary angiography, FFR, and IMR will be used to determine whether the inclusion and exclusion criteria are met, and then informed consent should be signed by the patient or the authorized person. The web-based randomization assigned those eligible patients 1:1 ratio to either the salvianolate or the placebo group. The secretary of the catheterization room accesses the website via account password and is responsible for randomization. Block randomization stratified by sex will be implemented and it is blind to those who enroll participants or assign interventions. In the immediate phase, the patients will receive an IMR test again after 30 min of intravenous infusion and the research nurses will record the IMR value. In the in-hospital follow-up period, complete blood count (CBC), serum electrolytes (potassium (K), sodium (Na), chloride (Cl)), liver function (alanine aminotransferase (ALT), aspartate aminotransferase (AST), bilirubin (BIL)), renal function (serum creatinine (Scr), blood urea nitrogen (BUN), uric acid (UA)), fasting glucose, lipid profile, cardiac troponin T/I (cTnT/cTnI), echocardiography, Seattle angina scale, quality of life scale, Holter electrocardiography, and 6-min walk test will be collected after continuous intravenous salvianolate 200 mg/day for 7 days.

All serious adverse events must be reported to the sponsor immediately or within 24 h in CRFs. The attending physicians are responsible for data entry. The data monitoring committee is responsible for data security and accuracy. Committee members ([name], [name], [name], and [name]) have access to the final dataset and periodically range check for data values.

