### End points

The primary end point will be the IMR change in the immediate phase during the coronary angiography procedure, and the secondary end points will be the total ischemic burden assessed by the Seattle angina scale, quality of life scale, Holter electrocardiography, and 6-min walk test after 7 days before discharge. The safety end point will be the abnormal blood tests and self-reported adverse events.

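### The withdrawal rule bars dosed non-completers from efficacy analysis while the Analysis section promises ITT of all randomised patients; neither rule is said to prevail, although the primary IMR change is complete on Day 1

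*Protocol article*

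**What the plan says.** All references are to the protocol article.

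- **Exclusion criteria during the follow-up periods.** Patients who have had at least one dose but "fail to complete the trial because of poor compliance or voluntary withdrawal should not be removed". The section then has withdrawals recorded and a visit arranged where possible, and concludes: "Although their data cannot be used for efficacy analysis, they can be used for safety analysis". The bar names no analysis set and no end point.
- **Analysis.** The section lists premature discontinuation, loss to follow-up and death as possible intercurrent events and adopts a treatment policy strategy. It plans two analyses. For the first, "ITT analysis includes all randomly assigned participants according to the treatment group to which they were originally assigned, regardless of the occurrence of intercurrent events". For the second, "Per-protocol analysis includes participants who complete the assigned therapy according to the trial protocol". It does not say which of the two is primary.
- **End points.** "The primary end point will be the IMR change in the immediate phase during the coronary angiography procedure".
- **Implementation and study procedures (text below Table 2).** "In the immediate phase, the patients will receive an IMR test again after 30 min of intravenous infusion". Table 2 schedules IMR at screening and in the immediate phase, both on Day 1, with none at Day 7.
- **Study design.** Treatment continues after the second IMR: "For the subsequent 7 days, the salvianolate group will be intravenously infused with salvianolate 200 mg/day", with saline given daily in the placebo group.

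**The concern.** A patient who is dosed, has both IMR readings and then withdraws on Day 3 must be left out of efficacy under one section and kept in under the other. Since neither rule is given precedence, the efficacy set could be settled after it is known who withdrew.

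The withdrawal rule also does not suit this primary end point. Nothing that happens on the ward can alter an IMR change already recorded in the catheterisation laboratory, so later withdrawal is no reason to set that value aside. Doing so would condition the primary comparison on an event that follows both randomisation and the outcome. If withdrawal is related to arm and to response, randomisation no longer protects the comparison.

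The per-protocol set has the same weakness for IMR, because it requires completion of therapy given after the outcome has been measured.

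**Working it through.** **Step 1. The two rules applied to one patient.** Take a randomised patient who receives the first infusion, has both IMR readings and withdraws voluntarily on Day 3.

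| Rule | Treatment of this patient's IMR change |
|---|---|
| Exclusion criteria during the follow-up periods | Not used for efficacy; safety only |
| Analysis, ITT definition | Used, in the assigned group |
| Analysis, per-protocol definition | Not used, because the 7-day course was not completed |

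The first two rows conflict. The third is not a conflict, but for IMR it excludes on the basis of doses given after the measurement.

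**Step 2. The plan's own figure.** The inputs, from Sample size, are α = 0.05, power 0.80, SD 20, means 20 and 40, Δ = −8, loss 10%.
- Effective difference in the formula: 20 − 40 − (−8) = −12.
- With a one-sided Z, as printed: n = 2 × (1.645 + 0.842)² × 20² / 12² = 34.35, so 35 per group, close to the stated 36.
- Allowing for loss: 35 / 0.9 = 38.9, so 39 per group and 78 in total, as stated.
- Working back: 39 × 0.9 = 35.1, so the plan budgets for about 35 analysable patients per group.

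**Step 3. Size if the withdrawal rule is followed.** The article gives neither the timing nor the cause of the 10% loss, so three cases are shown.

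*(a) No withdrawal after Day 1.* Nobody is dropped and the effect is nil.

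*(b) The whole 10% is post-Day-1 withdrawal unrelated to outcome.* About 4 of 39 are dropped per group, leaving 35. The standard error rises by √(39/35) = 1.056, or 5.6%. With difference 12 and SD 20, power goes from 84.3% to 80.7% one-sided (75.5% to 70.9% two-sided). There is no bias.

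*(c) Adverse illustration: selection in the salvianolate group only.* Suppose the 4 withdrawn patients had IMR changes D units worse than the 35 remaining, and placebo withdrawals were unrelated to outcome. The shift in the salvianolate mean is D × 4/39.
- D = 10: 10 × 4/39 = 1.03 units, or 1.03/8 = 13% of the 8-unit difference the plan calls clinically meaningful.
- D = 20: 20 × 4/39 = 2.05 units, or 2.05/8 = 26%.

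**Step 4. Simulation of the same kind of selection** (20,000 trials, 39 per group, SD 20, two-sided 0.05). Four patients were removed from the less-responding half of the salvianolate group and four at random from placebo.
- True difference −8: the mean estimate moves from −8.0 to −9.8, and rejection from 41.5% to 52.3%.
- True difference zero: the mean estimate is −1.7, and rejection rises from 4.9% to 5.9%.
- Equally selective removal of 4 from both groups (8,000 trials, true difference −8): the estimate stays at −8.0 and rejection falls from 41% to 37%, as under random loss.

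Bias therefore needs selection that differs between the groups.

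**The case against.** The strongest reply is that the Analysis section governs. It is the statistical part of the article, it names the strategy, and its ITT definition keeps everyone. The withdrawal section itself says these patients should not be removed, and its bar might be meant only for the per-protocol set. A reader might infer from the bar that valid primary data will be discarded and that the primary result will be a completers' comparison. The documents do not support that: it follows only if the withdrawal rule overrides the ITT definition, and nothing says that it does. But nothing says the reverse either. The bar refers to efficacy analysis without limit and is contrasted only with safety analysis. A later analysis plan could not satisfy both sentences.

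A reader might also infer that every dosed non-completer is barred. The section names poor compliance and voluntary withdrawal, and does not mention death or other loss.

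The bias figures are open to challenge, and the challenge stands. No figure in the article supports a 10 to 20 unit gap or selection in one group only. The trial is described as double-blind, the ward phase lasts only 7 days, and some of the 10% loss could be a missing second IMR, where there is no primary value to drop. The precision loss in case (b) is already within the sample-size allowance.

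The per-protocol point is the weaker part. That analysis runs beside ITT, and end-point-specific membership could be left to a fuller document. It is a refinement to make while the wording is being changed.

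**Conclusion.** The contradiction is established from the text and rests on no assumption: for dosed patients who withdraw or comply poorly, the two sections give opposite instructions on efficacy data, and neither is given precedence. For the primary end point the withdrawal rule is wrong as written, because the IMR change is complete on Day 1 and later events are no ground for removing it. The per-protocol definition shares that weakness for IMR.

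The size is unknown and may be nil. The 5.6% increase in standard error assumes that all of the planned loss is unrelated withdrawal after the second IMR. The shift of about 1 to 2 IMR units assumes 4 salvianolate withdrawals who did 10 to 20 units worse than those remaining, with no such selection in placebo; it shows what the rule could permit and does not predict what will happen. The case for correction rests on the contradiction over who enters the primary analysis, not on the simulated bias.

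**What to change.** 1. In Exclusion criteria during the follow-up periods, delete the bar on efficacy use, or limit it expressly to the per-protocol set.
2. In Analysis, state that the ITT analysis of IMR change is primary and includes every randomised patient with both readings, in the assigned group, whatever happens after the second IMR.
3. For IMR, define the per-protocol set by receipt of the assigned first infusion and both IMR readings. Keep completion of the 7-day course as a per-protocol condition for the Day 7 end points only.
4. For the secondary end points, include in the ITT analysis the assessments made at Day 7 in patients who stopped treatment early. Handle missing Day 7 values by the multiple imputation already planned. Do not put values from an earlier withdrawal visit in their place, since that would mix different time points.

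Items 1 to 3 are wording changes only: both IMR readings are already scheduled, and no patients or procedures are added. Item 4 may need some effort to obtain Day 7 assessments from patients who have stopped treatment. As recruitment began in January 2020, the change should go through the ethics committee and be recorded as the Amendments section requires, before anyone with access to allocation or outcome data decides the analysis set.
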